## Abstract

**Background:**

The primary aim of this study is to evaluate the effectiveness of different doses (intensity) of supervised exercise training — concomitant with lifestyle counselling — as a primary care intervention tool for the management of metabolic syndrome risk factors in low-active adults with one or more such factors (programme name in Catalan: Bellugat de CAP a peus).

**Methods/Design:**

Three-arm, randomized controlled clinical trial implemented in the primary care setting, with a duration of 40 weeks (16 weeks intervention and 24-week follow-up).

Adults aged 30 to 55 years with metabolic risk factors will be randomized into three intervention groups: 1) aerobic interval training (16 supervised training lessons) plus a healthy lifestyle counselling programme (6 group and 3 individual meetings); 2) low-to-moderate intensity continuous training (16 supervised training lessons) plus the same counselling programme; or 3) the counselling- programme without any supervised physical exercise.

The main output variables assessed will be risk factors for metabolic syndrome (waist circumference, blood pressure, and levels of plasma triglycerides, high-density lipoproteins and glucose), systemic inflammation, cardiorespiratory fitness, physical activity and sedentary behaviour, dietary habits, health-related quality of life, self-efficacy and empowerment. Economic factors will also be analysed in order to determine the cost-effectiveness of the programme. These variables will be assessed three times during the study: at baseline, at the end of the intervention, and at follow-up. We estimate to recruit 35 participants per group.

**Discussion:**

The results of this study will provide insight into the immediate and medium-term effects on metabolic risk and lifestyle of a combined approach involving aerobic interval training and a multidisciplinary behavioural intervention. If effective, the proposed intervention would provide both researchers and practitioners in this field with a platform on which to develop similar intervention programmes for tackling the repercussions of an unhealthy lifestyle.

**Trial registration:**

Clinical trials.gov. NTC02832453. Registered 6 July 2016 (retrospectively registered).

## Background

Metabolic syndrome consists of a cluster of risk factors for cardiovascular disease that comprises abdominal obesity, impaired glucose tolerance, hypertension and dyslipidemia. When these factors appear together the cardiovascular risk rises substantially. In Spain, the prevalence of metabolic syndrome is 42.1% in men and 32.3% in women, and it increases with age [1].

A considerable body of epidemiological evidence indicates that the most prevalent diseases in developed societies, including metabolic syndrome, are closely linked to lifestyle factors, notably smoking, unhealthy dietary habits, physical inactivity and stress. The increasing prevalence of metabolic syndrome and its negative impact on individuals and society has been mainly attributed to a decline in regular physical activity, an increase in sedentary behaviour and changes in dietary habits. Given that these factors are all modifiable they may be reversed through interventions focussing on behavioural change. Changes in lifestyle can have a positively effect on the prevalence of cardiovascular risk factors and, therefore, on that of metabolic syndrome and cardiovascular diseases [2].

In an attempt to tackle the problem of unhealthy lifestyles, the World Health Organisation (WHO) developed a Global Strategy on Diet, Physical Activity and Health, the aim of which was to control and prevent non-communicable diseases or their risk factors [3]. Physical activity has a key role to play in any such strategy. However, despite investment in the promotion of physical activity, the degree to which people engage in regular weekly exercise remains worryingly low. According to the Special Eurobarometer 412 [4], 54% of European Union citizens interviewed had not, during the previous week, done any physical activity of vigorous intensity, and 44% had not done any exercise of moderate intensity. In addition to the lack of moderate-to-vigorous physical activity, about two-thirds (69%) of respondents also stated that they spent between 2.5 and 8.5 h sitting during waking hours, and 11% sat for more than 8.5 h.

The health benefits of regular physical exercise in terms of preventing and treating many non-communicable diseases are well-established [5]. They include positive effects on single metabolic risk factors, such as normalization of blood pressure and improvements in body composition, hyperlipidaemia and insulin resistance [5]. Physical exercise also increases cardiorespiratory and muscular fitness. Regarding metabolic syndrome as a whole, Pattyn and colleagues [6] recently conducted a meta-analysis and concluded that dynamic physical exercise has beneficial effects on the majority of metabolic risk factors (abdominal obesity, high-density lipoprotein cholesterol (HDLc), systolic and diastolic blood pressure), as well as on other factors such as body mass index (BMI) or maximal oxygen uptake (VO_2max_). However, they also highlight that the most favourable modality/dose of exercise (dynamic versus static; low-to-moderate intensity versus high intensity) has yet to be fully elucidated.

Present guidelines for physical exercise as a healthy behaviour are based around continuous training methods (30–60 min/session, low-to-moderate intensity, 2–7 sessions per week) [5, 7, 8]. The WHO [9] recommends that individuals aged 18–65 should accumulate a minimum of 150 min per week of moderate-intensity physical activity or, alternatively, 75 min per week of vigorous physical activity, or a combination of both.

However, although moderate-intensity exercise is sufficient to reduce cardiovascular risk, it has been suggested that higher intensity exercise offers greater benefits [10–12]. Accordingly, the health setting has recently witnessed a growing interest in interval training methods, particularly high-intensity interval training (HIIT). When the aim of this method is to stimulate preferentially the aerobic system over the anaerobic one, it is referred to as aerobic interval training [13]. Aerobic interval training (AIT) consists of repeated bouts, either short (<45 s) or long (1 to 8’), of fairly high-intensity exercise (equal or superior to the maximal lactate steady-state velocity) interspersed with recovery periods.

To date, several studies have analysed the effects of AIT in individuals with cardiovascular risk factors or with diseases such as metabolic syndrome, ischaemic cardiopathy or cardiac insufficiency. Results from these studies suggest that AIT produces a greater improvement in VO_2max_ than does traditional continuous training (TCT). The effect has been described in recreationally active individuals [14], as well as in patients with coronary artery disease [15–17] or metabolic syndrome [18, 19]. It has also been shown that AIT reduces the prevalence of metabolic risk factors [15, 17, 19, 20]. The positive effects of AIT on metabolic risk factors involve changes in body composition, ventricular and vascular functions, plasmatic adiponectin and glucose intolerance. Studies comparing the effects of different training methods generally report better results after AIT and suggest that this method optimizes the time necessary to induce muscular, metabolic and cardiorespiratory effects in the medium and long term [17, 19, 20].

Although these studies support the efficacy of AIT for reducing metabolic risk factors, its effectiveness has yet to be fully demonstrated. One of the difficulties faced when seeking to replicate in practice the evidence obtained in controlled studies is that individuals are less constrained and become more responsible for their own compliance with physical exercise. As Rankin [10] states, physical exercise will have no benefits unless the individual actually does it. Accordingly, there is evidence to suggest that the most effective interventions, among those aiming to promote healthier behaviour, are those that not only involve scheduled physical activity and exercise but which also offer lifestyle counselling, including advice on dietary habits and how to reduce daily sedentary time, along with tools that can empower individuals towards behaviour change.

Detractors of high intensity exercise claim that HIIT is not an appropriate or sustainable form of exercise for public heath guidelines because it is unlikely to induce changes in the population as a whole [21]. It is argued that HIIT will be associated with negative feelings and lack of enjoyment, leading therefore to poor compliance. Biddle, for example, claims that as a public health tool, higher intensity exercise may not be better if people are less willing to do it [21]. However, AIT is a form of HIIT in which exercise intensity is not maximal. This feature may explain why, contrary to what might be expected given the low physical condition of the participants in some studies, AIT sessions have been well tolerated by sedentary individuals with or without concomitant diseases [17, 19, 20, 22, 23]. Indeed, no adverse effects have been reported [10], even in patients with heart failure [12], because the intensity is tailored to the individual.

In addition, participants in AIT interventions report greater satisfaction than do people in TCT interventions. This could be attributable to the variable nature of the session, in comparison with the monotony of TCT sessions, as well as to the fact that the intensity of intervals promotes a greater sense of challenge. These aspects reflect the potential of AIT to improve adherence to exercise interventions [23]. Although in some individuals AIT may trigger a feeling of displeasure and, hence, impair their confidence and adherence [21], factors such as the optimization of time spent on training sessions and the associated satisfaction of participants may contribute to the consolidation and long-term persistence of an active lifestyle.

To our knowledge, although the efficacy of AIT in relation to cardiometabolic risk factors has been established in several studies, there are no data on the effectiveness of AIT when implemented in conjunction with lifestyle counselling as an intervention in the primary care setting.

The primary aim of this study is to evaluate the effectiveness of different *doses* (intensities) of *supervised* exercise training (AIT and TCT), both concomitant with lifestyle counselling, and to compare this with lifestyle counselling (COU) alone as a primary care intervention tool for the management of metabolic syndrome risk factors in low-active adults with one or more such factors.

Secondary aims of the study are to investigate the effects of these interventions on systemic inflammation and adipose tissue function, cardiorespiratory fitness, physical activity and sedentary behaviour, dietary habits, empowerment related to health, self-efficacy in relation to physical activity and dietary habits, as well as the cost-effectiveness of the intervention with regard to health-related quality of life.

The study will also provide insights into the extent to which any observed changes persist in the medium term.

The general hypothesis is that among adults with risk factors for metabolic syndrome, those who participate in interventions designed to promote a healthy lifestyle through a combination of lifestyle counselling and supervised physical exercise of vigorous intensity will present greater improvements in terms of metabolic risk, physical condition, physical activity/sedentary behaviours and psychological parameters at the end of the intervention and at 24-week follow-up than will participants in interventions that combine lifestyle counselling with physical exercise of low-to-moderate intensity or those based exclusively on lifestyle counselling.

## Methods

### Trial design

This is a three-arm *(dose–response exercise*) randomized controlled clinical trial implemented in the primary care setting over a period of 16 weeks and with 24-week follow-up (Fig. 1).

**Fig. 1 Fig1:**
[figure not shown]
Bellugat flow chart

The study will include two supervised exercise groups with two different doses of exercise intensity (AIT and TCT), and a non-exercise control group (COU). All groups will be given lifestyle counselling.

### Participants

#### Eligibility criteria of participants

To be eligible, individuals should meet all the following inclusion criteria and none of the exclusion criteria.

##### Inclusion criteria

30 to 55 years-old.Having one or more risk factors for metabolic syndrome^1^ (waist circumference >94.5 cm for men and >89.5 cm for women; blood pressure ≥130/85 mmHg; triglycerides in plasma ≥150 mg/dL; HDLc in plasma <40 mg/dL for men and <50 mg/dL for women; fasting glycaemia ≥100 mg/dL).Low active (achieving less than 150 min/week of moderate-to-vigorous physical activity or to have not participated in any supervised exercise programmes for at least the last 24 weeks).Accept and sign written informed consent.Accept the randomized group assignment.

##### Exclusion criteria

Morbid obesity (BMI ≥ 40).A past/current history and/or evidence through physical examination or laboratory findings of significant cardiovascular, respiratory, neuromuscular or psychiatric disease/disorder.Diseases/disorders that may contraindicate performing physical exercise or a stress test [7].

#### Enrolment, screening and allocation

Participants will be recruited through primary healthcare centres, including physician referrals and advertisements through the media, community centres and electronic mailing. Interested individuals will be invited to an information session, where an in-depth detailed explanation of the study requirements and expectations will be given. Any questions will be answered and doubts clarified. Potential eligibility will be checked/confirmed by interview, obtaining information about age, past and current physical activity, medical history and medication use. Eligible participants who wish to participate in the study will be asked to sign written informed consent.

After providing written informed consent individuals will be given an identification number. Participants will be allocated to one of the two supervised physical exercise groups (AIT or TCT) or to the control group (COU), using a computer generated randomized list which allocates at random the identification number of the participant to a treatment group. The allocation sequence will be generated by the IDIAP and will be conducted without influence of the principal investigators.

#### Blinding

Due to the nature of the intervention, blinding of participants will not be possible as each of them will be aware of the kind of physical exercise they are engaged in. However, during data analysis researchers will be blinded to the intervention allocated to each participant.

#### Sample size

At least 105 individuals will be recruited for this study. Based on previous studies [20], a sample of this size would provide a beta risk of 0.2 and an alpha risk of 0.05 when using a bilateral contrast to detect a mean change in waist circumference of 6.0 cm (SD 5.3). Assuming a 20% drop-out rate at follow-up, we aim to recruit 35 individuals for each intervention group.

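### The sample-size statement does not follow from its printed inputs (6.0 cm with SD 5.3 needs 14 per arm for 80% power, not 28), and the 6.0 cm is not tied to any between-arm contrast

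*Protocol article*

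**What the plan says.** The Sample size section of the protocol article contains the trial's only power statement. It opens with "At least 105 individuals will be recruited for this study" and then, citing earlier work, makes this claim for that number: "a sample of this size would provide a beta risk of 0.2 and an alpha risk of 0.05 when using a bilateral contrast". The effect on which the claim rests is worded as "to detect a mean change in waist circumference of 6.0 cm (SD 5.3"). The section closes with: "Assuming a 20% drop-out rate at follow-up, we aim to recruit 35 individuals for each intervention group".

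The section does not say which arms are compared, whether 6.0 cm is a difference between arms or a change within one, which test was assumed, or whether alpha is shared between contrasts.

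The Trial design section describes three arms. The general hypothesis at the end of the Background is between arms: AIT participants "will present greater improvements in terms of metabolic risk" and other outcomes "than will participants in interventions that combine lifestyle counselling with physical exercise of low-to-moderate intensity or those based exclusively on lifestyle counselling". The Statistical methods section sets the significance level at 0.05. It plans an intention-to-treat analysis of everyone with a baseline assessment, with missing outcomes filled by last observation carried forward (LOCF).

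**The concern.** Every input needed to check the calculation is printed, so this is not a matter of detail held in an analysis plan. A standardised effect of 6.0/5.3, above 1.1, is very large, and 28 completers per arm is about twice what it calls for at 80% power. Either an input is misdescribed or the number came from a calculation other than the one reported.

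The second difficulty is what the 6.0 cm measures. The hypothesis is about differences between arms, all of which receive counselling and two of which train on the same schedule of sessions. A within-arm change of 6.0 cm would say nothing direct about the AIT–TCT or AIT–COU difference.

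At stake is whether a reader can tell what between-arm difference the trial can detect. From the present text that is not possible.

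**Working it through.** **Inputs (Sample size section).** Difference 6.0 cm; SD 5.3 cm; two-sided alpha 0.05; power 0.80; drop-out 20%; 35 recruited in each of three arms.

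**The step that reproduces.** 35 × 0.8 = 28 completers per arm, 28/0.8 = 35, and 3 × 35 = 105. The article does not print 28, but the drop-out allowance implies it.

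**The step that does not.** Take 6.0 cm as the difference between two arms and 5.3 cm as the SD of the analysed variable.
- Standardised difference: d = 6.0/5.3 = 1.132.
- Normal approximation: n per arm = 2(1.960 + 0.842)²/d² = 2 × 7.85/1.282 = 12.2, so 13.
- Two-sample t-test: n = 13.3, so 14 per arm. After drop-out 14/0.8 = 17.5, so 18 per arm and 54 in total.
- Three pairwise contrasts at alpha/3 (0.0167), t-test: n = 17.8, so 18 per arm. After drop-out 18/0.8 = 22.5, so 23 per arm and 69 in total.

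**Power of the planned size for 6.0 cm with SD 5.3 (t-test).**

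| Analysed per arm | Two-sided 0.05 | alpha/3 |
|---|---|---|
| 28 | 98.6% | 95.8% |
| 35 | 99.7% | 98.7% |

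At 28 per arm beta is therefore about 0.014, against the stated 0.2.

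**Other readings that use only the printed figures.**
- One-sample (pre–post) change: n = 8.2, so 9 per group.
- Three-group ANOVA with a 6 cm range: total 37 (means 0, 0, 6) to 48.2 (means 0, 3, 6), so 13 to 17 per arm.
- Two-sample t-test at 90% power: n = 17.4, so 18 per arm.

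None gives 28.

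**Readings that add unstated assumptions.** Suppose 5.3 is the SD at a single visit. With pre–post correlation ρ, the SD of change is 5.3 × √(2(1 − ρ)).

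| ρ | Alpha | SD of change (cm) | n per arm (t-test) | Recruited per arm |
|---|---|---|---|---|
| 0 | 0.05 | 7.50 | 25.5, so 26 | 33 |
| 0.1 | 0.05/2 | 7.11 | 28.0, so 28 | 35 |
| 0.2 | 0.05/3 | 6.70 | 27.6, so 28 | 35 |

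So 35 per arm can be reached, but only by combining a different meaning for 5.3, a low correlation and a multiplicity adjustment. The text states none of the three.

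**What 105 delivers if 5.3 cm is the SD of change.** Difference detectable with 80% power (t-test):

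| Analysed per arm | One contrast at 0.05 | alpha/3 |
|---|---|---|
| 28 (completers) | 4.0 cm | 4.7 cm |
| 35 (all, with LOCF) | 3.6 cm | 4.2 cm |

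The last row is nominal: it treats carried-forward values as observed data. For assumed between-arm differences of 3, 2 and 1 cm, power at 28 per arm and two-sided 0.05 is 55%, 28% and 11%. The article gives no expected AIT–TCT difference, so these figures only illustrate the range.

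**The case against.** Four points can be made for the plan.

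- **A route to 105 exists.** As shown above, a single-visit SD with low correlation and adjusted alpha gives exactly 28 and 35. This stands to the extent that the number cannot be called impossible. It does not rescue the text, which attaches the SD to the change and mentions neither a correlation nor a multiplicity adjustment. The defensible claim is that 105 cannot be reproduced from what is printed.
- **The term for a mean change may be loose wording** for a difference in change between arms. That is possible, and the cited study is not available to settle it. A reader might infer that the 6.0 cm is certainly a within-arm change and hence the wrong quantity; the article does not support that. What it supports is that the quantity is undefined and no contrast is named. Neither meaning rescues the statement: as a between-arm difference, beta 0.2 is wrong; as a within-arm change, the calculation does not address the hypothesis.
- **The error is in the safe direction.** On the stated inputs the trial is larger than necessary. This stands. A reader might infer that the trial is underpowered, but the mismatch does not show that, and the power figures for 1 to 3 cm rest on assumed differences.
- **The practical harm is not documented.** The article has no figure showing that 6.0 cm is implausible between two active programmes, or what proportion of participants will have a raised waist. Eligibility requires only one of five risk factors, which permits normal waists but does not say how many. Arguments of that kind should not carry the point.

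**Conclusion.** The point holds in this form. The claim of beta 0.2 at 6.0 cm with SD 5.3 is wrong on the plan's own inputs: 14 per arm would suffice (18 at alpha/3), and the implied 28 give 98.6% power (95.8% at alpha/3). Separately, the effect is not defined as a between-arm difference, although the hypothesis is stated between arms. The arithmetic assumes a two-sample t-test with equal arms and takes 5.3 as the SD of the analysed change, as the text reads. If 5.3 is a single-visit SD, the required number depends on a correlation that the article does not give. The finding concerns the stated justification; it is not evidence that 105 is too few.

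**What to change.** Keep 105 and rewrite the Sample size section.

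1. Delete the statement that beta is 0.2 at 6.0 cm with SD 5.3.
2. Name the between-arm contrast or contrasts that the calculation serves (AIT–TCT, AIT–COU or both), and say whether alpha is shared.
3. Say whether 5.3 cm is the SD of change or of a single visit.
4. State what the design delivers. If 5.3 cm is the SD of change, wording could be: 'With 35 randomised and 28 completing per arm, an SD of change of 5.3 cm and two-sided alpha of 0.05, the trial has 80% power for a between-arm difference in waist-circumference change of about 4.0 cm for a single contrast (about 4.7 cm if three contrasts share alpha).' If the calculation is meant to match the intention-to-treat analysis with LOCF, give the figures for 35 per arm (about 3.6 cm and 4.2 cm) and label them nominal. If 5.3 is a single-visit SD, recompute with a stated pre–post correlation.
5. Give the power for one or two smaller AIT–TCT differences.

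The cost is text only, with no change to recruitment, randomisation or analysis. The downside is that limited power for smaller differences becomes visible, for example about 55% for an assumed 3 cm at 28 per arm.

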#### Ethical implications

The study will be carried out in accordance with the principles of the Declaration of Helsinki, and subsequent revisions, as well as with the Guidelines for Good Practice in Primary Care Research of the Jordi Gol Primary Care Research Institute (IDIAP).

The research protocol has been reviewed and approved (P15/122) by the Institutional Board (CEIC) of the IDIAP, and written informed consent will be obtained from all participants prior to their inclusion in the study. Specifically, all individuals will give their written informed consent in accordance with the principles of the Declaration of Helsinki and the dispositions established in Spanish law (Chapter II, article 7, Royal Decree 223/2004 of 6 February 2004); the consent form will specify that participation in the study is voluntary and that participants may withdraw at any time. This information will be provided both orally and in writing.

In this study, only researchers and health care professionals will have access to participants’ data.

The study methods are consistent with the CONSORT guidelines for the reporting of randomized trials [24].

